#### Secondary Study Parameters - Cost-Effectiveness

Cost categories that will be included are: (1) health care costs (primary and secondary care, complementary care, and home care); (2) lost productivity costs (absenteeism from paid and unpaid work, and presenteeism); and (3) participant costs (informal care and other care services paid for by participants themselves). For the valuation of health care usage, lost productivity, and informal care, Dutch standard costs from the Dutch costing guidelines [61] will be used. Medication use will be valued using prices of the Royal Dutch Society for Pharmacy. Patient and family costs other than informal care will be valued using self-reported prices. For the valuation of absenteeism from paid work, the friction cost approach will be used. We will estimate the cost-effectiveness of rTMS compared to sham rTMS after 12 months of follow-up from a societal perspective. The following effect measures will be included in the economic evaluation: (1) severity of OCD symptoms (Y-BOCS), (2) quality-adjusted life-years (EQ-5D-5L with Dutch reference values [52]). Linear regression analyses will be used to estimate cost and effect differences between both conditions while adjusting for confounders if necessary. Incremental cost-effectiveness ratios (ICERs) will be calculated by dividing the difference in the mean total costs between the treatment groups by the difference in mean effects between the treatment groups. Bias-corrected and accelerated bootstrapping with 5000 replications will be used to estimate 95% CIs around the cost differences and statistical uncertainty surrounding the ICERs. Uncertainty surrounding the ICERs will be graphically presented on cost-effectiveness planes. Cost-effectiveness acceptability curves will also be estimated, showing the probability that the intervention is cost-effective in comparison with control for a range of different ceiling ratios, thereby showing decision uncertainty [62].

#### Secondary Study Parameters - Neuroplasticity

We will first examine the effects of ERP and rTMS across multiple levels, using both blood-based and neuroimaging markers of neuroplasticity. For the neuroimaging component, we will use multimodal techniques, including both structural and functional MRI scans acquired at baseline and posttreatment. Data will be analyzed using hypothesis-driven Bayesian region of interest models and exploratory general linear model-based whole-brain analyses. All scans will undergo appropriate preprocessing using established open-source neuroimaging pipelines (eg, fmriprep [63] and mrtrix3 [64]). Structural and functional imaging data at baseline will also be examined as potential predictors of treatment outcome.

For the biomarker component, we will analyze genomic, proteomic, and extracellular vesicle–derived measures collected at baseline, posttreatment, and follow-up. Analyses will combine genome-wide and targeted biomarker data using both Bayesian and conventional statistical approaches. Longitudinal changes in proteomic and circulating biomarker levels will be modeled using linear mixed-effects models to account for repeated measures. Genetic association and polygenic risk score analyses will assess baseline genetic variation as a predictor of molecular profiles and clinical outcomes.

#### Exploratory Moderators and Mediators of Treatment Response

The exploratory outcomes and parameters that will be investigated as modifiers of treatment response include expectation of outcome, participant treatment adherence, circadian rhythm, sleep disorders, and medication status. Depending on the results, additional moderator and mediator analyses will be carried out.

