This rationale is further supported by emerging evidence suggesting that the effects of rTMS are state-dependent [22], meaning that the cognitive and behavioral context during stimulation may influence treatment efficacy. In OCD specifically, this may be particularly relevant given the rigidity and chronicity of compulsive behaviors. ERP and rTMS likely target overlapping but distinct mechanisms: ERP promotes inhibitory learning, cognitive flexibility, and behavioral adaptation through exposure [23], whereas rTMS may facilitate cortical excitability and network plasticity [11]. Combining these approaches may therefore create conditions that are more favorable for therapeutic learning and more durable symptom change than either intervention alone [20,24]. This approach is also consistent with findings from other psychiatric disorders. In depression, there is evidence that psychotherapy and noninvasive brain stimulation could outperform neuromodulation monotherapy [25]. In anxiety disorders, active rTMS combined with psychotherapy showed significantly greater symptom improvement compared to sham rTMS [20]. Although evidence for combined treatment in OCD remains limited, these findings provided an important rationale for investigating this strategy in a treatment-resistant OCD population. An additional advantage of this design was that all participants received an active and potentially beneficial intervention, as prior insufficient response to ERP does not necessarily imply that more intensive ERP-based approaches are ineffective [26]. This may also positively influence recruitment and reduce dropout in this severely affected patient population. In summary, the use of LF rTMS over the pre-SMA alongside ERP therapy reflects the direction of clinical and ongoing experimental treatment in the field.

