### Intervention

Treatment consists of 4 sessions per week in which each rTMS session is immediately followed by a 90-minute ERP session. This offers the logistical benefit of catching up on a missed treatment during a treatment week. The treatment follows an adaptive design, offering a minimum of 20 sessions to all participants with a possible extension of 4 or 8 sessions for participants who continue to show improvement and/or are motivated to continue therapy (see decision rules below) for optimal treatment effect. Change in symptoms is measured weekly during the treatment by administration of the Y-BOCS-II [37] to obtain a severity score after every 4 individual sessions. After 4 weeks of combined treatment, the process of the treatment is evaluated with the patient and one of the clinicians to decide if treatment should be continued after the 5th week. The decision process on (dis)continuation always follows shared decision making and is independent of treatment allocation; in case of doubt, the case is to be discussed in the weekly indication & treatment meeting. Participants who, after clinical evaluation, feel that they can still benefit from treatment can continue. If clinicians and participants agree that treatment will not be beneficial anymore or if participants worsen during treatment, treatment is discontinued. At the end of week 6, we again monitor progress using the same criteria, allowing participants who continue to show steady (partial) response the opportunity to undergo a seventh week of treatment, amounting to a maximum of 28 sessions per participant. This design allows participants who are experiencing protracted and slowly accruing benefit from the repeated combined sessions to maximize their treatment effect; and it accounts for the slow and linear benefit of repeated rTMS sessions that has been observed in adults with OCD, who still improve at or after 20 sessions [38,39]. Additionally, it allows for participants not benefiting enough from the treatment to exit the study and prevent unnecessary burden.

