### Co-Intervention: Exposure in Vivo With Response Prevention (ERP)

Prior to the first rTMS-ERP treatment session, 2 ERP preparation sessions without TMS are planned. These sessions are used to motivate participants, reestablish the working mechanisms of ERP, and achieve commitment for active participation in exposure sessions and homework. In addition, participants are helped to define their treatment goals and to link these goals to specific exposure exercises, which can be practiced in either supervised exposure sessions following TMS or at home in unsupervised exposure exercises. ERP is provided according to standard treatment protocols for OCD. Sessions last 90 minutes, which is slightly longer than usual, permitting ERP exercises to take place beyond the confines of the therapist’s office. For this study, a treatment manual has been developed (largely based on the protocol used during the previous TIPICCO trial [19]), consisting of practical information, the time schedule, the agenda to be used in all sessions, and all forms that participants fill in during the treatment (including, for example, those for goals and exercises). Each ERP session follows a similar structure, including a reflection on the prior treatment session, discussing homework exercises, and registering whether homework has been conducted according to plan. Early in the session, clinician-supervised exposure commences in the clinic or outside, depending on the exercise. Clinicians motivate the participant, safeguard against subtle forms of avoidance behavior, and question the participant about the dysfunctional cognition (ie, the prediction the participant expects to occur). When possible, a more realistic alternative cognition is formulated. At the end of the exposure session, homework exercises are planned. ERP is provided by trained and well-supervised clinicians with varying experience and background (registered health care and clinical psychologists, psychologists at entry-level, resident psychiatrists, and behavioral therapy assistants). The clinicians have supervision and intervision every 2 weeks to share experience, discuss exposure exercises, and stagnation in the therapy. Multiple clinicians take responsibility for the treatment of one patient. Doing so enables a 4/wk treatment schedule, decreases the impact of clinician-variables on outcome, and, according to our experience in the TIPICCO-trial, facilitates a strict focus on the exposure during treatment sessions. At the end of the combined rTMS-ERP treatment (after 20, 24, or 28 sessions; see for details adaptive design above), 2 relapse-prevention sessions are scheduled. In these sessions, the possibility of relapse is discussed, and a personalized relapse prevention plan is made. Such a plan is advised in treatment guidelines, helping the participant to recognize early signs of relapse and to take action if necessary. Subsequently, we perform weekly telephone calls for 4 weeks to stimulate continued self-exposure in daily life. After these 4 weeks of self-exposure, we finish with an evaluation session. During the subsequent 1-year naturalistic follow-up phase, participants are allowed to participate in new treatments (but not rTMS) if necessary.

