Blood sampling at baseline, directly posttreatment, and at 3-month follow-up is performed to establish markers of treatment-induced neuroplasticity and predictors of treatment response.Pre- and posttreatment MRI scans to analyze ERP and rTMS-induced effects on multiple levels in the brain, using innovative multimodal neuroimaging.Pretreatment structural and functional MRI scans to assess brain structure and network activation and connectivity to predict treatment response.

Exploratory variables:

Patient adherence to treatment protocol, as measured using the Patient Exposure and Response Prevention Adherence Scale (PEAS; [53]) and its relationship to treatment outcome. This scale is carried out by the therapists as part of usual treatment.Difference between responders and nonresponders on circadian rhythm and other sleep disorders at baseline as defined by the Holland Sleep Disorders Questionnaire (HSDQ), as a possible prognostic marker for response [54,55].The relationship of demographic and clinical variables (gender, age, age of onset, medication status), preexisting comorbidities (ie, comorbid tics, depression, anxiety, and autism), and treatment history to the treatment outcome. A simplified Dutch version of the Mini-International Neuropsychiatric Interview (MINI) for *DSM-5*-diagnoses is used to confirm OCD diagnosis and establish current comorbidity [56]. To specifically evaluate symptoms of comorbid autism spectrum disorder, the Dutch version of the Autism Spectrum Questionnaire (AQ-NL) [57] is administered.The Y-BOCS-II symptom checklist [37] is used to categorize symptom dimensions and examine treatment effects and underlying mechanisms in different OCD subgroups.Measuring the exact stimulation location as ascertained and recorded by neuronavigation on 3 separate sessions (session 1, 10, and 20) will allow us to map the variation in achieved location in relation to treatment outcome.Variation in treatment expectancy (7-item credibility and expectancy questionnaire) [58] and blinding success (1-item question “in which condition do you think you were?”) in relation to treatment outcome.

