### Blinding

Participants, ERP therapists, and those carrying out clinical and cognitive assessments are blinded to treatment conditions. The rTMS treatment administrators are not blinded due to the technical nature of this treatment; however, they are instructed not to disclose treatment allocation to participants, therapists, or blinded assessors.

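### Therapist-rated ERP adherence is listed as an exploratory modifier of treatment response, although its ratings in the combined phase follow randomization and could be affected by rTMS

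*Protocol article*

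**What the plan says.** The section Exploratory Moderators and Mediators of Treatment Response in the protocol article states that the parameters "investigated as modifiers of treatment response include expectation of outcome, participant treatment adherence, circadian rhythm, sleep disorders, and medication status". It then adds: "Depending on the results, additional moderator and mediator analyses will be carried out".

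Outcome Measures (exploratory variables) defines the adherence item as "Patient adherence to treatment protocol, as measured using the Patient Exposure and Response Prevention Adherence Scale (PEAS; [53]) and its relationship to treatment outcome". On who rates it, the article says: "This scale is carried out by the therapists as part of usual treatment". It gives no rating time points. The sleep questionnaire in the same list, by contrast, is tied explicitly to baseline.

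On the order of treatment, Intervention says: "Treatment consists of 4 sessions per week in which each rTMS session is immediately followed by a 90-minute ERP session". The co-intervention section adds that ERP also occurs before any stimulation: "Prior to the first rTMS-ERP treatment session, 2 ERP preparation sessions without TMS are planned". Whether the PEAS is scored in those two sessions is not stated.

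**The concern.** A modifier in the usual sense is a characteristic fixed before treatment, so that the arms can be compared within its levels and randomization still protects the comparison. Medication status and sleep at baseline fit that description. Adherence over 20 to 28 combined sessions does not, because it is observed while the treatment is being given.

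The trial's own rationale makes an effect of stimulation on ERP engagement plausible. Of rTMS and ERP, the introduction says: "Combining these approaches may therefore create conditions that are more favorable for therapeutic learning". If part of any rTMS benefit runs through better engagement with exposure, holding adherence fixed takes that part out. If an unmeasured trait, such as motivation, drives both adherence and outcome, patients at the same adherence level in the two arms are no longer comparable. At stake is a misleading secondary message about who benefits from rTMS. The main efficacy result is not at stake.

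**Working it through.** **The plan's own figure.** Sample Size Calculations gives a standardized effect of 0.4, two-sided alpha 0.05, power 0.8 and 2:1 allocation. Recalculation gives 74 sham + 148 verum = 222, against the stated 75 + 150 = 225. Power at 75/150 is 0.807, and 225/0.9 = 250. The figure reproduces and nothing below changes it. I use 0.40 SD as the reference effect, with negative values favouring rTMS (lower Y-BOCS).

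**Timing.** The PEAS is rated by therapists during ERP, and each combined ERP session follows rTMS. Ratings in that phase therefore come after both randomization and stimulation. Only the two preparation sessions precede rTMS, and nothing says the PEAS is limited to them. That the ratings are post-stimulation is an inference from these statements, but a strong one.

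**Step 1: adherence-specific arm effect when rTMS shifts adherence uniformly.** Let A be arm, U an unmeasured trait and M adherence (within-arm variance 1).

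- M = aA + bU + error
- Y = dA + gM + cU + error
- Total effect T = d + ga
- Since E[U | A, M] = b(M − aA), the arm effect at fixed M is d − abc = T − a(g + bc)

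Assumed values, none of them from the documents: T = −0.40, b = 0.5, c = −0.4, g = −0.3. Then g + bc = −0.3 − 0.2 = −0.5.

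| Shift a (SD) | Direct effect d = T − ga | Arm effect at fixed adherence |
|---|---|---|
| 0 | −0.40 | −0.40 |
| 0.2 | −0.34 | −0.30 |
| 0.3 | −0.31 | −0.25 |
| 0.5 | −0.25 | −0.15 |

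At a = 0.3 the gap from −0.40 to −0.25 has two parts. The pathway through adherence accounts for 0.3 × 0.3 = 0.09, which is a change of estimand. The shared cause U accounts for 0.3 × 0.5 × 0.4 = 0.06, which is selection bias.

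If adherence has no effect on outcome (g = 0), only the second part remains: at a = 0.3, −0.40 + 0.3 × 0.2 = −0.34.

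A simulation of 1.5 million patients per setting agrees (−0.401, −0.300, −0.248, −0.152 for the table; −0.340 for g = 0). With a = 0.3 and g = −0.3, a median split gives about −0.30 in both halves. In every uniform-shift setting the simulated arm-by-adherence interaction is essentially zero (at most 0.004).

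**Step 2: when a false interaction appears.** Suppose rTMS also weakens the link from U to adherence. Assume M = 0.3A + sU + noise (SD 0.8), with s = 0.6 in sham and s = 0.3 or 0 in verum. Assume Y = −0.4A − 0.5U + noise, so the true effect is −0.40 for everyone and adherence does nothing. The within-arm slope of Y on M is −0.5s/(s² + 0.64).

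- Sham: −0.30/1.00 = −0.30
- Verum, s = 0.3: −0.15/0.73 = −0.21, so the interaction is about 0.09
- Verum, s = 0: slope 0, so the interaction is 0.30

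Simulated interactions are 0.093 and 0.301. The median-split arm effects (high/low adherence) are −0.25/−0.45 and −0.12/−0.60, although no modification exists.

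**The case against.** The strongest reply is that the article writes out no arm-by-adherence model, interaction or subgroup. Outcome Measures speaks only of adherence and its relationship to outcome. The word for modifiers may also be loose, since sleep is on the same list and is described elsewhere as a prognostic comparison of responders with nonresponders. The section heading includes mediators, and this is a short exploratory paragraph in a condensed article whose analysis plans are to be preregistered. All of this is fair and keeps the point conditional: it bites only if arm effects are examined by adherence level. It does not remove the point, because the sentence places adherence among the modifiers, while further mediator work is left to depend on the results.

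A reader might go further and infer that adherence-specific arm effects will be biased, perhaps by 15–38% (0.40 falling to 0.34 or 0.25 SD, from shift × slope of 0.2 × 0.3 or 0.3 × 0.5). The documents do not support that. They give no effect of rTMS on adherence and no adherence–outcome slope. If the slope is the causal effect of adherence, the subtraction gives a direct effect, which is a different estimand and not an error. With no shift the bias is zero.

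Nor does a uniform shift make rTMS look weak specifically in adherent patients. It lowers the effect equally at every level and leaves the interaction at zero. That pattern requires rTMS to change who adheres.

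Unblinded rating is not the issue either: "Participants, ERP therapists, and those carrying out clinical and cognitive assessments are blinded to treatment conditions". Blinding guards against biased scoring, but it does not stop a real change in adherence.

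**Conclusion.** The point holds as a small improvement to an exploratory analysis. Adherence is given the role of modifier, but its combined-phase ratings are post-randomization and could respond to assignment. If arm effects are examined by adherence level, they can be biased when rTMS changes adherence, and a false interaction can arise when rTMS changes who adheres.

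The size is unknown. The illustrations (0.40 SD reading as 0.30 to 0.15 SD for shifts of 0.2 to 0.5 SD; false interactions of 0.09 to 0.30) rest wholly on assumed path sizes. The conclusion also rests on two readings: that the PEAS is rated mainly in the combined phase, and that being listed as a modifier means comparing arms across adherence levels. The primary ANCOVA adjusting for baseline Y-BOCS I and the intention-to-treat analyses do not depend on it.

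**What to change.** In the analysis plan to be preregistered:

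- Limit modifier (arm-interaction) tests to variables measured before the first rTMS session: sleep and circadian measures, medication status, and expectancy if it is taken before treatment.
- Take PEAS adherence off that list and report it by arm as a process outcome.
- Analyse it as a candidate mediator, adjusting for baseline covariates and stating the assumption of no unmeasured confounding between adherence and outcome.
- State when the PEAS is rated.

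The cost is a change of wording and a little more analysis work, with no new data. The trade-off is that no adherence-specific arm effect would be claimed.

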### Ethical Considerations

This clinical trial was approved by the Institutional Ethics Board of Amsterdam University Medical Center on the 10th of March 2022 (2021.0670 - NL78930.029.21) and is registered at clinicaltrials.gov (NCT05331937), on April 15, 2022, last updated on January 15, 2026. All participants give both verbal and written informed consent before completing any study-related procedures. The data will be deidentified and, following the completion of data collection, will be transferred to and stored in a secure data repository with safeguards to protect patient confidentiality. Participants receive a modest reimbursement for participation in the research assessments (not for the treatments), as well as compensation for travel and parking expenses.

### Data Monitoring

Each clinical site oversees the internal quality of study implementation, including data collection, documentation, and study completion. All sites follow a standardized data quality management plan. Before initiating data collection, site principal investigators (site-PIs) and the independent monitor verified that appropriate safety protocols were established at each site. The PI, site-PIs, and other core project members, including the researcher with lived experience (representing the patient foundation), met to review study protocols, emphasizing outcome definitions, study design, serious adverse event (SAE) reporting procedures, informed consent processes, and documentation standards prior to the start of the study. All staff receive training, including a good clinical practice (GCP) course, to carry out assessments, ensuring familiarity with data collection methods, procedural workflows, and SAE reporting requirements. The trial consortium (PI, site-PI’s, core trial researchers, and patient representative) meets monthly to monitor the trial progress.

